### DATA VARIABLES

- Primary dependent variables; the infants’ venous haemoglobin and haematocrit value will be measured at 24 hours of life. Polycythemia, Neonatal jaundice and need for phototherapy/exchange transfusion
- Secondary dependent variables: neonatal anaemia, maternal primary post partum haemorrhage.
- Independent variables: Delayed cord clamping (control) and Umbilical cord milking (intervention).

#

[figure not shown]

Excluded (n= )

- Multiple gestation (n= )
- Declined consent (n= )
- Major congenital abnormalities (n= )
- Red cell isoimmunisation(n= )
- Positive serology HIV/Hep/VDRL (n= )
- Tight nuchal cord (n= )
- Ante partum haemorrhage (n= )
- Need for neonatal resuscitation (n= )

Assessed for eligibility (n= )

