# ABSTRACT

**Background:** The placenta is a useful reservoir of fetal blood that can serve to alleviate anaemia of prematurity, prevalent in almost all premature neonates(1). Immediate cord clamping is a routine practice worldwide despite current evidence on the benefits of providing placental transfusion to the new born(2). Umbilical cord milking and delayed cord clamping are two such strategies providing for placental transfusion. Major obstetric and gynaecological societies are now recommending delayed cord clamping(3,4). Umbilical cord milking is a cost effective intervention and can be considered for faster placental transfer when delayed cord clamping cannot be performed such as when a neonate requires resuscitation. The findings of this study will inform strategies to reduce neonatal anaemia in a country that is one of 15 responsible for over 2/3^rd^ the world’s preterm births and its subsequent complications specifically anaemia(5).

This study aims to evaluate that umbilical cord milking is comparable in benefits to delayed cord clamping and can be beneficial to premature neonates where every second after birth is essential.

**Objective:**  To determine the effects of umbilical cord milking versus delayed umbilical cord clamping on selected haematological and clinical parameters in preterm neonates.

**Methodology:** Randomized controlled trial, single blind. Mother-baby pairs at premature gestation (<37weeks) who meet the selection criteria, will be randomized to either Umbilical cord milking (n=140) or Delayed cord clamping (n=140). UCC will be performed≥60 seconds after delivery and UCM will be performed 4times.

The primary outcomes of the study will be haemoglobin and haematocrit levels determined 24 hours after birth. The secondary outcomes will be neonatal jaundice and maternal primary postpartum haemorrhage.

**Study setting:** Kenyatta National hospital labour ward, maternity theatre and neonatal intensive care unit.

**Data collection tool**: Interviewer administered questionnaire will be used by the principal investigator and 2-research assistants.

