# Study objectives

Research question:

Is there a difference in haemoglobin, haematocrit and neonatal jaundice between preterm infants who will undergo umbilical cord milking versus delayed cord clamping?

Broad objective:

To determine the effects of umbilical cord milking versus delayed cord clamping on haemoglobin, haematocrit, and neonatal jaundice of preterm neonates.

Primary objectives:

Among preterm neonates at 28-36 weeks who will undergo umbilical cord milking versus delayed cord clamping at vaginal or caesarean delivery, to:

1. Determine and compare the mean haemoglobin and haematocrit values at 24 hours of life.

Null hypothesis: There is no difference in the mean haemoglobin and haematocrit values 24 hours after birth comparing pre term neonates delivered at 28-36 weeks who will undergo umbilical cord milking versus delayed cord clamping.

1. Determine and compare the incidence rate of neonatal polycythemia at 24 hours of life.

Null hypothesis: There is no difference in the incidence rate of neonatal polycythemia at 24 hours after birth comparing pre term neonates delivered at 28-36 weeks who will undergo umbilical cord milking versus delayed cord clamping.

1. Determine and compare the incidence rate of neonatal jaundice within the first week of life.

Null hypothesis: There is no difference in the incidence rate of neonatal jaundice within the first week of life comparing pre term neonates delivered at 28-36 weeks who will undergo umbilical cord milking versus delayed cord clamping.

Secondary objectives:

Among preterm neonates at 28-36 weeks who will undergo umbilical cord milking versus delayed cord clamping at vaginal or caesarean delivery, to:

1. Determine and compare the incidence rate of neonatal anaemia within the first 24 hours of life.
2. Determine and compare the incidence rate of maternal primary post partum haemorrhage within 24 hours of delivery.

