### DATA ANALYSIS

Descriptive statistics will be reported to describe the study population. Proportions will be reported for categorical data, the mean and standard deviation will be reported for continuous normal data while the median and Inter-quartile range [IQR] will be reported for non-normal data. Proportions in each study arm will be compared for the secondary outcome.

Data will be analysed using STATA analytical package version 13,while presentation will be inform of charts and graphs for descriptive statistics while tables will be used for the presentation of inferential statistics. All statistical tests will be performed at 5% level of significance (p value<0.05) while odds ratios and corresponding 95% confidence intervals will be reported for regression analysis.

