# STUDY LIMITATIONS

The study lacks addition of another control arm to undergo immediate cord clamping. Given the recent evidence on benefits of placental transfusion and adverse effects of ICC there was not enough clinical equipoise to have assigned an ICC arm.

The time period of follow-up is focused on short term outcomes due to timeline limitations, it would be more enriching to have long term outcomes. This cohort can therefore be followed up in another study evaluating the long term outcomes.

The study is not primarily designed to assess possible adverse effects of placental transfusion, however previous studies have disproved a correlation between placental transfusion interventions and PPH, neonatal polycythemia and hyperbilirubinaemia.

It will not be possible to measure the amount of blood actually transfused from the placenta into the newborn child.

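### The protocol gives three conflicting lists of primary outcomes. They agree on haemoglobin and haematocrit, but not on whether polycythaemia, jaundice and phototherapy/exchange transfusion are primary.

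*Protocol*

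**What the plan says.** Three sections of the protocol define the primary outcomes.

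- **Abstract, Methodology:** "The primary outcomes of the study will be haemoglobin and haematocrit levels determined 24 hours after birth". It continues: "The secondary outcomes will be neonatal jaundice and maternal primary postpartum haemorrhage".
- **Study objectives, Primary objectives:** "Determine and compare the mean haemoglobin and haematocrit values at 24 hours of life"; "Determine and compare the incidence rate of neonatal polycythemia at 24 hours of life"; "Determine and compare the incidence rate of neonatal jaundice within the first week of life". Each of these three objectives has its own null hypothesis.
- **Data Variables:** the primary dependent variables are venous Hb and Hct at 24 hours, followed by "Polycythemia, Neonatal jaundice and need for phototherapy/exchange transfusion".

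Three other sections bear on the point. Data Analysis states: "All statistical tests will be performed at 5% level of significance". Sample Size uses Hb only. Study Limitations states: "The study is not primarily designed to assess possible adverse effects of placental transfusion", and the same sentence goes on to name postpartum haemorrhage (PPH), polycythaemia and hyperbilirubinaemia.

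**The concern.** Jaundice cannot be both secondary (Abstract) and primary (Study objectives, Data Variables). Polycythaemia is primary in two lists and absent from the Abstract's outcomes. Phototherapy/exchange transfusion is primary in one list only. A reader of the final report could not tell from this protocol which clinical results were meant to carry a primary claim, and the choice could be made once the results are known.

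The larger lists also raise the chance of a false-positive primary result, because each test is at 5% and this document ranks no outcome above another. They give primary status to binary outcomes that were never sized, in a trial that says it was not primarily designed to assess such effects.

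**Working it through.** **1. The lists side by side**

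| Outcome | Abstract | Study objectives | Data Variables |
| --- | --- | --- | --- |
| Hb at 24 h | primary | primary | primary |
| Hct at 24 h | primary | primary | primary |
| Polycythaemia | not listed | primary | primary |
| Jaundice | secondary | primary | primary |
| Phototherapy/exchange transfusion | not listed | not listed | primary |
| Number of primaries | 2 | 4 | 5, or 6 if the last row is split |

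Other sections fit the short list better. Data Analysis speaks of comparing proportions for the secondary outcome, although the longer lists make proportions primary. The overview in Appendix IV names only Hb and Hct in its objective. The follow-up form (Appendix III, Part V) has boxes for jaundice and polycythaemia but none for phototherapy or exchange transfusion.

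**2. The protocol's own sample size**

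Inputs from Sample Size: SD 2, difference 0.7, z values 0.84 and 1.96, ratio 1:1.

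n per arm = 2 × 2² × (0.84 + 1.96)² / 0.7² = 8 × 7.84 / 0.49 = 128.

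This matches the stated 128. Adding 10% gives 256 × 1.10 = 281.6, against the stated 280, which is a rounding difference. The size is therefore sound for one two-sided 5% test of Hb. Power is 80% with 128 evaluable per arm and 83% with 140.

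**3. Familywise error for each list**

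Assume that all null hypotheses are true and that any one significant primary counts as success. With k independent tests the error is 1 − 0.95^k.

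The tests are not independent: Hb and Hct come from the same blood count, and polycythaemia is defined from Hct. The protocol gives no correlations, so these were assumed: Hb-Hct 0.8 to 0.95; polycythaemia with Hb or Hct 0.4 to 0.6; among jaundice, phototherapy and exchange transfusion 0.4 to 0.7; all others 0.1 to 0.2. The correlated figures come from multivariate-normal simulation with 1,000,000 draws.

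| List | k | Independent | Assumed correlations |
| --- | --- | --- | --- |
| Abstract | 2 | 9.75% | 6.5-7.8% |
| Study objectives | 4 | 18.5% | 14.3-16.2% |
| Data Variables | 5 | 22.6% | 17.6-20.0% |
| Data Variables, last item split | 6 | 26.5% | 19.8-23.4% |

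**4. What the binary outcomes could show (illustration)**

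The protocol gives no base rates. Assume 50% for jaundice, 5% for polycythaemia, and 140 × 0.9 = 126 evaluable per arm. The arcsine formula with 80% power at two-sided 5% requires 2·arcsin√p₂ − 2·arcsin√p₁ = 2.80/√(126/2) = 0.353. Jaundice would have to move from 50% to 67%, or polycythaemia from 5% to 15%.

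**5. Cost of keeping several primaries**

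With Bonferroni and the same SD and difference, the Hb comparison would need 156, 183 or 191 evaluable per arm for two, four or five primaries. At 128 per arm its power would be 71%, 62% or 59%.

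**The case against.** The lists do share a core. Hb and Hct come first in all three and are the only outcomes named in the Study Design statement and the Appendix IV objective, and Hb alone drives the sample size. A reader might infer that the primary outcome is wholly open. The documents do not support that: what is unsettled is which clinical outcomes join Hb and Hct.

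A reader might also infer that the trial as a whole carries a familywise error of about 15-23%. That range fits only the four- and five-outcome lists; the Abstract's pair gives about 6-10%. No section says that one significant result makes the trial positive, and the objectives set out separate hypotheses. The independence figures are upper ends that these outcomes cannot reach.

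A multiplicity rule may stand in a statistical analysis plan that is not shown, so its absence here is not a fault in itself. Co-primary outcomes with an alpha allocation would also be legitimate.

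All of this limits the size of the point. None of it makes the Abstract, the Study objectives and Data Variables agree, and an analysis plan could not do so without overriding at least one of them.

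**Conclusion.** The point holds as an internal contradiction that must be resolved before analysis. It rests on the text alone: three primary lists of two, four and five (or six) outcomes, with jaundice moving between secondary and primary.

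The size of the error inflation is conditional. It is about 6-10%, 14-19% or 18-23% for the three lists, and up to 26.5% if phototherapy and exchange transfusion are counted separately. These values assume that all nulls are true and that any one significant primary counts as success. The upper ends assume independence, and the lower ends rest on assumed correlations. The detectable differences for jaundice and polycythaemia only illustrate assumed base rates. The stated sample size is not in question for Hb.

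**What to change.** Make the Abstract, the Study objectives and Data Variables agree:

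- Name venous Hb at 24 hours, the only outcome that was sized, as the single primary outcome, tested at two-sided 5%.
- Make Hct the first secondary outcome, tested at 5% only if Hb is significant.
- List polycythaemia, jaundice, phototherapy/exchange transfusion, anaemia and PPH as secondary or safety outcomes, reported with 95% confidence intervals and no confirmatory claim.
- Align the null hypotheses with this order.

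The cost is wording in the protocol, and in the registry entry if one has been made; the Training section plans registration after approval. The downside is that fewer results can be called primary. The 128 per arm and the total of 280 stand. If the sponsor prefers several primaries, the protocol should state the alpha allocation and resize the trial accordingly.

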## Enrolment

Figure 2: CONSORT diagram: study enrolment, intended randomization.

## Analysis

Analysed for primary and secondary outcomes (n= )
♦ Excluded from analysis (give reasons) (n= )

Analysed for primary and secondary outcomes (n=)
♦ Excluded from analysis (give reasons) (n= )

Vaginal delivery (n= )

Caesarean delivery (n=)

## Allocation

Randomized delayed cord clamping (n= )

Randomized to

Umbilical cord milking (n= )

Randomized to

Delayed cord clamping (n= )

Randomized to

Umbilical cord milking (n= )

Randomized (n= )

# DATA COLLECTION, MANAGEMENT AND ANALYSIS

After obtaining formal permission and ethical clearance, the study will be conducted at Kenyatta national hospital. The eligible participants will sign an informed consent. Respective data collection will be done in the Reproductive health labour ward, postnatal wards, paediatric wards and the neonatal ICU. Follow up data will be collected via phone call for the patients that have been discharged from hospital early.

Data will then be entered onto a REDCap electronic database with inbuilt consistency and range checks. No patient-identifiable information will be collected on the questionnaires or entered on to the REDCap database. The database will be password protected and only authorised personnel will have access to the data. The questionnaires will be stored in lockable cabinet and only the PI or the persons granted permission by the PI will have access. Automated haematology analyser will measure haemoglobin and haematocrit, by colorimetric principle.

The principal investigator and the recruited study research assistants will carry out the data collection. A structured survey questionnaire will be used to gather obstetrical and medical details and a venous blood sample will be taken from the neonate for laboratory investigations.

Training of research assistants will take place over the duration of one week; initially they will observe the process of obtaining informed consent and filling of the questionnaires. Thereafter they will work under supervision until the principal investigator is satisfied. The principal investigator will constantly review the questionnaires for completion. The intervention will be carried out by the midwife who will be trained by clinical tutorials and video tutorials.

The data monitoring will be continuous and the statistician will alert the principal investigator of any overt differences in the two groups. The study will be halted if there is evidence of significant statistical advantage in whichever group, to avoid denying the corresponding group an advantageous intervention.

LABORATORY PROCEDURES:

COLLECTION AND TRANSPORT:

All neonatal blood samples will be collected using a 23-gauge needle from a peripheral vein amounting to 0.5mls by the attending paediatric resident as per the hospital protocol. Blood will be collected in EDTA tubes (BD Vacutainer®).The blood sample will be transported in a blood transport box by the research assistant to the Kenyatta national hospital laboratory and analysed for ‘complete blood count’: Hb, Hct, MCV, mean cell haemoglobin concentration (MCHC). Complete blood counts will be analysed using the automated haematology analyser. The results will be collected by the research assistant and the data filled into the data collection form by the research assistant.

QUALITY CONTROL

The analyser equipment will be calibrated with standard calibrators. The internal quality control will be set daily every morning, done by running a know quality control sample along with tests, to confirm the validity of the values of the tests.

INFECTION CONTROL

All infection control protocols will be adhered to throughout the study procedure .This will include aseptic technique for all invasive medical procedures, hand hygiene and use of personal protective equipment for all medical procedures.

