**Analysis plan**: Levels of haemoglobin and haematocrit of newborn infants following umbilical cord milking will be compared to those of newborns who undergo delayed cord clamping using unpaired students T- test and a P value <0.05 for significance. Prevalence will be compared using proportions and chi squared test of independence. Measurements of excess risk will be estimated using relative risk at 95%confidence interval that excludes the null value will be considered significant. Intention to treat analysis will be used.

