# SAMPLE SIZE:

Using the formula for sample size calculation (Chow S, Shao J, Wang H. 2008).

$$n=\frac{r+1}{r}\frac{{{SD}^{2}\left( Z_{\beta}+Z_{\alpha/2} \right)}^{2}}{d^{2}}$$

Where:

SD **=** standard deviation from a previously published study=2

d=expected mean difference between the groups

r=ratio for the groups= 1:1

$Z_{\beta}$**=**standard normal variation for level of power=80% power is 0.84

Z$\alpha/2$= standard normal variation for level of significance= 1.96

In a similar study done by Katheria AC(24), using the mean value for haemoglobin for UCM and DCC, we get our sample size as follows:

$$n=\frac{1+1}{1}\frac{{2^{2}\left( 0.84+1.96 \right)}^{2}}{{0.7}^{2}}$$

n= 128 per arm

To account for attrition bias an additional 10 percent will be added to the total sample size.

Therefore a total sample size of 280 will be required for the study.

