**DSMB OVERSIGHT RESPONSIBILITIES**

Oversight of the trial is provided by the DSMB.Meetings will take place to monitor on safety of patients and signals of efficacy, futility or harm. The DSMB members will have a first meeting before study is commenced. A meeting will be constituted in case of any adverse event and a final meeting on conclusion of the study. In case of unacceptable safety concerns/results occur, the board can recommend termination of the study. The safety of the participant is paramount.

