**DATA ANALYSIS PLANS**

The statistician will not be blinded and data monitoring will be continuous, he will alert the principal investigator of any overt differences in the two groups. The study will be halted if there is evidence of significant statistical advantage in whichever group, to avoid denying the corresponding group an advantageous intervention.

In case of SAE, a report will be forwarded to ERC and study halted immediately pending clearance.

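### The protocol orders a halt on statistical significance under continuous unblinded monitoring, with no boundary, number of looks or endpoint; read with its only stated level (unadjusted 5%), this inflates the false-positive rate.

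*Protocol*

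**What the plan says.** The halting rule appears twice. The section on data collection, management and analysis states: "The data monitoring will be continuous and the statistician will alert the principal investigator of any overt differences in the two groups". It goes on: "The study will be halted if there is evidence of significant statistical advantage in whichever group". Appendix IV (data analysis plans) repeats the halt and adds: "The statistician will not be blinded and data monitoring will be continuous, he will alert the principal investigator of any overt differences".

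Neither place gives a threshold, a number or timing of looks, an endpoint, or a minimum number of infants before the rule applies.

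The only significance level in the protocol is 5%:
- The data analysis section says "All statistical tests will be performed at 5% level of significance (p value<0.05").
- The abstract compares haemoglobin and haematocrit "using unpaired students T- test and a P value <0.05 for significance".
- The sample size section uses the same level for one fixed test: "standard normal variation for level of significance= 1.96", with "standard normal variation for level of power=80% power is 0.84".

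Appendix IV asks the DSMB to watch for signals of efficacy, futility or harm. The meetings it lists are one before the start and then: "A meeting will be constituted in case of any adverse event and a final meeting on conclusion of the study". No efficacy review is scheduled during recruitment.

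**The concern.** A 5% test keeps its 5% error rate only if it is done once. If the data are tested repeatedly and the trial stops at the first p<0.05, chance alone gives many opportunities to stop, and the error rate grows with the number of looks. Such a rule also tends to stop when the observed difference happens to be high, so the reported effect is too large. The unadjusted p-value and confidence interval after such a stop are invalid.

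The rule also sends arm differences to the principal investigator, who takes part in recruitment, consent, monitoring of deliveries and data collection. The body meant to judge efficacy signals has no meeting planned for that purpose.

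At stake is a result that the justification section wants to use to support cord milking as routine practice for all preterm neonates. Once the trial has stopped, the missing infants cannot be recovered.

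**Working it through.** **Inputs from the protocol.** SD 2, difference 0.7, two-sided z = 1.96, power z = 0.84, ratio 1:1 (sample size section); 140 per arm (study design); unpaired t-test at p<0.05 (abstract, data analysis). The unit g/dl is taken from the dummy table of haematological outcomes.

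**The plan's own figure.** n = [(r+1)/r] × SD² × (0.84 + 1.96)² / d² = 2 × 4 × 7.84 / 0.49 = 128 per arm, as stated. Adding 10%: 256 × 1.1 = 281.6, close to the stated 280. Power for a single test is 80.0% at 128 per arm and 83.4% at 140 per arm. The design is therefore a fixed-sample design with one 5% test and no allowance for interim looks.

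**Assumption needed.** The protocol says only that monitoring is continuous, so the schedule must be assumed and the range shown. Seven looks corresponds to monthly looks over the stated period, December 2017 to June 2018.

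**False-positive rate.** Trials were simulated with no true difference, SD 2, up to 140 per arm, a two-sided t-test at 0.05 at each look, stopping at the first significant look (20,000 trials per schedule, haemoglobin only).

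| Looks | False-positive rate |
|---|---|
| 1 (final only) | 4.9% |
| 2 | 8.3% |
| 3 | 10.7% |
| 5 | 14.5% |
| 7 | 16.6% |
| 14 | 22.5% |
| 28 | 27.6% |
| every pair from 30 per arm | 23.5% |
| every pair from 20 per arm | 26.0% |
| every pair from 10 per arm | 31.4% |
| every pair from 5 per arm | 35.2% |

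**Exaggeration.** With a true difference of 0.7, the mean estimate among significant trials and the mean number analysed per arm over all trials are:

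| Looks | Mean estimate (g/dl) | Mean n per arm |
|---|---|---|
| 1 | 0.77 | 140 |
| 3 | 0.89 | 90 |
| 7 | 0.99 | 72 |
| 28 | 1.16 | 56 |
| every pair from 20 per arm | 1.00 | 58 |
| every pair from 10 per arm | 1.12 | 52 |

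The single-analysis value of 0.77 is the right comparator, because selecting on significance already adds 0.07. Seven looks adds a further 0.99 − 0.77 = 0.22, and 28 looks a further 1.16 − 0.77 = 0.39.

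**Check of the fix.** One interim at half the information (70 per arm, 140 infants) gives two correlated test statistics with correlation √0.5. The expected z at the end is 0.7 / (2 × √(2/140)) = 2.93, and at the interim 2.93 × √0.5 = 2.07. Integrating the bivariate normal distribution:
- p<0.001 at the interim and 0.05 at the end: overall error 5.02%, power 83.4%.
- 0.005 then 0.048: overall error 4.99%, power 83.1%.

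Both hold the error at 5% and lose almost none of the 83.4% power of the single test.

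**The case against.** **The 0.05 is not written beside the halt.** It comes from the statement in the data analysis section that covers all tests, and that section mainly describes final reporting. This stands as a limit on the figures. It does not rescue the rule: if 0.05 is not meant, the mandatory halt has no threshold at all.

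**A boundary may sit in a statistical analysis plan or DSMB charter that is not shown.** That is possible, but the protocol does not leave the matter open. It fixes continuous looks and a compulsory halt on significance, in two places, and a boundary elsewhere would contradict that text.

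**No single error rate can be claimed.** A reader might quote 17 to 31% as the effect of the rule. The documents do not support that as a bound: three looks gives about 11%, and looks from 5 per arm give 35%. Continuous monitoring points to the higher part of the range, but the schedule remains assumed.

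**Compounding over outcomes.** A reader might multiply the error as if a second primary outcome were independent. Haematocrit comes from the same blood count as haemoglobin, and polycythaemia is defined from haematocrit, so independence does not hold. With an assumed correlation of 0.90 to 0.95 between haemoglobin and haematocrit, testing both after every pair from 10 per arm gives roughly 37 to 40%. Watching more outcomes raises the error, by an amount the documents do not fix.

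**The DSMB is not expressly excluded.** One might infer that it is bypassed. The text says only that the investigator is alerted, and adverse events such as postpartum haemorrhage could well trigger DSMB meetings. What stands is that no efficacy review is scheduled there.

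**Bias through the investigator is limited.** The trial is already open-label at delivery, and laboratory staff are blinded for the blood count. Knowledge of trends matters more for enrolment and for jaundice and estimated blood loss than for haemoglobin.

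**Conclusion.** The rule is wrong as written and should be corrected before it is applied. It requires a halt on significance under continuous, unblinded monitoring, without a boundary, number of looks, endpoint or minimum information, in a trial sized for one 5% test.

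If the protocol's only level (0.05) applies at each look, the false-positive rate for haemoglobin is roughly two to six times the planned 5%: about 11% at 3 looks, 17% at 7, 28% at 28, and 26 to 31% when tested after every pair from 20 or 10 per arm. At the design difference, schedules of 7 looks or more move the mean significant estimate from 0.77 to about 0.99 to 1.16 g/dl.

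These figures rest on the assumed schedules, on normal data with SD 2, and on haemoglobin alone. It would be too strong to say that no valid inference could follow an early stop. The unadjusted p-value and interval would be invalid, but adjusted inference is possible if every look has been recorded.

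**What to change.** Delete the halt on continuous significance from the data collection, management and analysis section and from the data analysis plans in Appendix IV. Then choose one of two courses:

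1. Allow no efficacy stopping.
2. Pre-specify a named primary endpoint (for example haemoglobin at 24 hours), a small fixed number of looks (for example one, at about 140 infants with 24-hour results) and a boundary. Suitable boundaries are Haybittle-Peto (p<0.001 at the interim, 0.05 at the end) or O'Brien-Fleming (about 0.005, then 0.048).

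Under the second course, the statistician prepares the interim for the DSMB only, and the meeting is added to the DSMB section of Appendix IV. Under either course, remove the alert to the principal investigator and withhold arm-level interim results from the investigator and site staff. Safety oversight by the DSMB stays as it is.

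The cost is wording in three places, with no change in sample size. The downside is that a real difference is less likely to stop the trial early.
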